### 2.4. Exposures

The four major indoor (emissions from cooking and cleaning products) and outdoor pollutants (engine emission and wood combustion) emitted from the sources below have been selected as comparators to clean air as they are known to contribute substantial fractions to indoor and outdoor air.

Diesel exhaust: Previous studies demonstrate a clear negative effect on cardiopulmonary health [37,38] and there is evidence of neurological impacts of diesel exhaust in young healthy volunteers [39,40]; therefore, it is a pollutant of interest in this study;Wood smoke: Wood smoke is a prevalent indoor and outdoor air quality issue in the UK [41]; in the last 10 years, its emissions have substantially offset the decrease in particulate matter (PM) from other sources, increasing by 33%, and it is likely to continue increasing in the medium-term [42]; therefore, identifying the impact on human cognitive health is of necessity at this critical juncture. The physical and chemical characteristics of the emissions from wood burning can vary widely depending on the fuel, burn condition, appliance, and dilution [43]. Here, we have selected a condition that enables us to produce stable and repeatable exposures for the participant group;Cooking emissions: The significant contribution of cooking aerosol to indoor/urban air quality has recently emerged as an important topic within the aerosol community [34], but there is little solid evidence on its potential health impacts. A recent study did suggest that ultrafine aerosols from frying meat resulted in altered electrical brain activity in human subjects [44], warranting its further investigation here;Cleaning products: Limonene, a household cleaning product ingredient, known for its citrus scent and effective dirt retention, is commonly found in indoor air at concentrations ranging from 20 to 50 
μ
g m^−3^ in residential buildings [45,46]. Peaks exceeding 70 
μ
g m^−3^ occur during cleaning episodes [47]. The presence of limonene and similar volatile organic compounds (VOCs) in indoor air raises health concerns, potentially causing sensory irritation, headaches, organ damage, or cancer [48]. Minimal evidence exists linking SOAs formed from household cleaning products to adverse cognitive effects. We have chosen limonene in the first instance to separate it from the other components across the multitude of cleaning products, whilst recognising its presence across lemon-fragranced products.

The study is designed to attempt to discriminate between the responses to exposure to 4 common pollutant types and a clean air control. The pollutant types have been selected as they make significant contributions to ambient air quality in indoor and outdoor situations. It is not possible to conduct exposures to emissions generated under all possible operating conditions of the individual sources. However, selection of a set of standard operating conditions for each source enabling the stable and repeatable generation of each pollutant emission type can enable comparison of the responses to exposure to each of the classes of pollutant. A description of the standard operating procedures and the chemical and physical characterisation of each source is the subject of a manuscript in preparation.

Participant exposures will be conducted at the Manchester Aerosol Chamber (MAC) facility. The MAC facility is part of the ATMO-ACCESS atmospheric simulation chamber network. It is an 18 m^3^ fluorinated ethylene propylene Teflon bag housed in a temperature- and humidity-controlled enclosure and illuminated by a combination of wavelength-filtered arc and halogen lamps. Clean inlet air is ensured by scrubbing with a series of filters and conditioners. Particle and gas levels are controlled either by injection of individual components or by coupling to a variety of real pollutant sources [49]. This facility as well as the techniques and specific instruments employed here have been used in many previous chamber studies [50,51,52]. For each pollutant mixture, a full characterisation will be conducted to identify the exact chamber conditions and experimental setpoints to achieve target pollutant concentrations to within acceptable limit. All experimental setpoints are computer-controlled and continuously monitored, ensuring participant safety, and enabling repeatability.

The aim is to achieve desirable PM (particle matter) mass concentrations (150 
μ
g m^−3^) for human exposure studies. The chemical and physical characterisation of particle and gas phase pollutants from each source was conducted using online instruments, and a protocol has been developed for generating desirable and reproducible PM mass concentrations from each source. Detailed information on this process is the subject of a manuscript in preparation. A brief description is provided below.

Diesel exhaust: For the generation of diesel emissions, we selected a diesel generator (Manufacturer: Lister Petter) that can provide representative and safe levels of PM/NO_*X*_. The engine is run on idle for 5 min and then the emissions are transferred to the chamber until the desired PM concentration is reached;Wood smoke: To replicate a representative wood combustion condition in the atmospheric environment, a commercial Ecodesign-ready wood-burning stove (Esse 175F; sd) is employed in this study. Wood samples are burned inside the stove, positioned outdoors adjacent to the laboratory building, and using ambient air. Exhaust emissions are sampled from a port in the 125 mm diameter flue and drawn into the chamber via an ejector diluter (Dekati^®^ eDiluter^™^ Pro; Dekati Ltd., Kangasala, Finland);Cooking emissions: The cooking process is carried out in a cooking chamber (approximately 0.7 m^3^). The aim is not to replicate any particular recipe, but to generate combustion emissions that will be components of some recipes, but that will be distinct from wood burning or diesel exhaust. To reduce variability, ingredients are kept limited, using 100 mL of olive oil and 2 pieces of pork chops to generate particles under standard frying conditions using an induction hob at a single setpoint. Once pollutants have accumulated sufficiently within the cooking chamber, clean air from our chamber system is used to flush all cooking-related pollutants into the aerosol chamber;Cleaning products: Since limonene is a major compound found in cleaning products, we utilize it as a representative compound to produce secondary organic aerosols (SOA). For this study, we employ 130 ppb of limonene and 50 ppb of O_3_ to generate particles. Under these conditions, all the O_3_ is consumed, resulting in a residual limonene concentration of approximately 40 ppb, well within the safe range.

Participants will undertake a 60-minute exposure to a controlled concentration of common air pollutants in addition to a clean air exposure to act as a control. Participants will be fitted with a mask covering the nose and mouth (VariFit^™^ NIV non vented mask; Sleepnet Corporation, Hampton, NH, USA) attached to the aerosol chamber via a plastic pipe. The mask will use a two-way valve (Anti-pollution T-piece directional valve) allowing participants to inhale air from the chamber without forced air pressure and exhale into the surrounding room, avoiding contamination of the chamber air mixture. See Figure 2. As each participant completes pre- and post-exposure measures for each air mixture, including a clean air control, they serve as their own control. This approach helps mitigate possible individual differences in lung size and exposure uptake. Additionally, as participants are only included in the study with no underlying significant lung issues, and are at rest during exposure, it is unlikely there would be significant differences in tidal volume [53], further supporting the argument that variations in exposure due to breathing rate or body size are not a significant concern in the study.

A review of adverse event reporting from previous wood smoke and diesel exhaust exposure chamber studies utilising higher pollutant concentrations showed no evidence of adverse events. See Supplementary File S2 for full details.

### 2.5. Physiological Measures

#### 2.5.1. Spirometry

Spirometry will be a safety measure in this study. Volunteers will be asked to perform spirometry, to achieve 3 reproducible forced expiratory volume (FEV1) and forced vital capacity (FVC) measurements according to the American Thoracic Society/European Respiratory Society guidelines [54].

#### 2.5.2. Blood Tests

Blood will be taken as part of the assessment of inflammatory response. This will be plasma and RNA samples 5 mL (3 bottles pre exposure and 3 bottles on visit b), a total of 30 mL per participant per visit.

These collected samples will be centrifuged and transported to Imperial College Health Care NHS trust for analysis and storage. These will be stored for 2 years under their Human Tissue Authority License number 12,275.

Once analysis has been completed, any additional samples will be stored in biobanks for up to 30 years if participants have consented to this optional/additional section in the ICF. If a participant does not wish to have their samples stored in a biobank, this will not affect their participation in the study. It is expected that these biobanked samples will be accessible to researchers for further analysis in the future.

We intend to complete analyses for the following effects. Systemic inflammation will be assessed by measuring plasma concentrations of TNF-
α
, IL6, IL8, and C-reactive protein (CRP). BBB disruption, neuroinflammation, and neuronal injury will be assessed by determination of S100 calcium-binding protein B (S100B), Glial fibrillary acidic protein (GFAP), and Neurofilament light chain (NF-L), respectively, using commercial ELISAs.

#### 2.5.3. Nasal Lavage

Participants will undertake nasal lavage with 15 ml pre-warmed normal saline solution (0.9% NaCl). Sterile solution will be instilled into the participant’s nose whilst their head is flexed and chin towards their chest. There will be a total of 10 sprays in one nostril, whilst the other is closed off. This will be repeated four times and then, using a glass beaker, the fluid is collected. The whole process is then repeated with the other nostril for a total of 50 sprays in each nostril. The sample is then decanted into a centrifuge tube and centrifuged for 10 mins at 800× *g* at 4 °C.

We will employ this lavage method to ensure the collection of pure samples from the nasal lining fluid, enabling the investigation of damage-associated molecular patterns (DAMPs) as an early signal driving downstream immune response.

The nasal lavage samples will then be transported to Imperial College Health Care NHS trust for analysis and storage. These will be stored for 2 years under their Human Tissue Authority License number 12,275. These samples will then be destroyed as per the terms of the license.

We intend to complete analyses for the following effects. Cell free lavage will be analysed for markers of acute neutrophilic inflammation (IL-6, IL-8) and activation (Myeloperoxidase, lactoferrin) to provide an in vivo marker of the capacity of each of the aerosols to induce upper airway inflammation, paralleling an approach adopted previously [55]. In addition, lavage fluid antioxidant concentrations, ascorbate urate and the GSH/GSSG ratio, will be determined according to established assays [56].

### 2.6. Cognitive Measures

#### 2.6.1. Dementia Assessment

The General Practitioner Assessment of Cognition [57] (GPCog) is a screening tool for global cognitive impairment seen in those with dementia. The Participant Examination assessment (see Supplementary File S3) will be completed as part of eligibility screening. Briefly, participants are given a name and address to immediately repeat and remember. Participants are then asked to provide the exact day, complete two diagrams highlighting clock time, and tell the experimenter something that has happened in the news in the past week. Participants then recall the name and address they were asked to remember at the start. Usually, a score of 8 or below would involve additional information (Step 2: Informant Interview) from an informant, i.e., a family member who would know the participant and their current functioning compared to previous years. As we will not have access to an informant, participants will be allowed one error, so a score of 8 or 9 will indicate that participants are cognitively intact and can continue with the study.

#### 2.6.2. Cognitive Tasks

For cognitive assessment, we will utilise five tasks—one standardised manual task and four internally designed computer tasks. Two of the computer tasks will integrate novel elements into previously used paradigms and two will adhere to more commonly used methodologies, ensuring alignment with established research. This approach combines standardised rigour with innovative, internally developed tasks, providing a comprehensive evaluation of cognitive domains. A summary of the five tests is detailed in Table 2 and further description is given below. The full methodology of each task is provided in the Supplementary Materials (File S4).

The Purdue Pegboard Test [58] (PPT) is a manual test not requiring a computer. The other four cognitive tasks will require a Windows 10 computer running Matrix Laboratory (MATLAB) version R2022a [59]. These four tasks are in the format of a MATLAB script utilising the Psychophysics Toolbox version 3.0.18 [60]. The five tasks are described in more detail below.

Spatial *n*-Back Task: A working memory task using spatial locations of stimuli. This is a measure of participant ability to hold multiple pieces of information in the brain at one time and recall that information when necessary;Face Identification Task: A selective attention task using particularly distracting face stimuli. This is a measure of cognitive control, a facet of executive function, specifically, participant ability to ignore distracting stimuli and focus on task goals;Purdue Pegboard Test: This is a standardised test to measure of motor control, specifically participant hand and finger dexterity to manoeuvre small objects;Expression Recognition Task: A Go/No-Go task using affective facial stimuli. This is to measure socio-emotional cognition, specifically, participant ability to identify the emotion expression of a human face at speed;Psychomotor Vigilance Task: A simple reaction time task. This measures both sustained attention, i.e., participant ability to focus their attention for a sustained period of time, and psychomotor speed, i.e., speed of their response to changes in the visual field.

### 2.7. Data Analysis

Data generated by this study will be analysed using longitudinal statistical modelling designed to account for the repeat measures in individual subjects (e.g., general estimating equation or random effects modelling, depending on the extent and nature of any missing or partial data). This will describe and account for changes in pre-exposure measures over time, comparing the effects of the different air pollution exposures to the clean air control.

Cognitive subscales will be entered into this process separately, to aid in pairing aerosols with undesirable changes identified in each cognitive domain. Our goal is to ensure an equal representation of biologically male and female participants, acknowledging potential sex-dependent effects of exposure. Consequently, biological sex will be entered as a covariate of interest during analysis.

In addition to ranking cognitive impacts in relation to the exposure sources, these data will be related to biomarkers of systemic and neuro-inflammation/injury to test the secondary hypothesis that acute cognitive effects and more severe downstream neurological impacts reflect underlying inflammatory processes.

Specifically, our primary and secondary end points are as follows:

Primary end point:

Evidence of impairment in cognitive function post exposure as measured by any of these cognitive tasks compared to clean air:Difference in the Approach bias measured via the Expression Recognition Task post pollutant exposure;Change in the Cognitive Control response time post pollutant exposure;Change in the 2-back discrimination index post pollutant exposure.

Secondary end point:

Change in performance on any of these cognitive tasks post pollutant exposure compared to clean air:Psychomotor Vigilance Task;Purdue Pegboard Test;Evidence of inflammatory or immune signals post exposure to pollutants compared to clean air;Change in lung function post pollutant exposure compared to clean air;Change in DNA post pollutant exposure compared to clean air.

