## 2. Methodology

### 2.1. Trial Design

This is a single-centre double-blind study of the effects of mixed air pollutants on the cognitive function of healthy human volunteers with a family history of increased risk of dementia. Participants will all undertake sequential controlled exposures to four air pollutants and clean air as control exposure, i.e., a repeated measures design. Cognitive testing, biological sampling, and physiological tests will be carried out before and after each exposure. The study design is outlined in Figure 1.

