### 2.3. Participant Volunteers

This study will aim to recruit 45 clinically healthy individuals aged 50 and above with a family history of dementia. See Appendix A for full inclusion and exclusion criteria. Recruitment began in May 2023 and due to significant challenges, as explained in detail in the discussion section, the originally planned sample size was reduced to 15 participants. The study is currently ongoing, and data collection is expected to be completed by the end of 2023. See Table 1 for study timeline.

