#### 2.3.1. Power Calculation

Based on effect size and variance from a currently unpublished study [35] looking at cognitive load and attention (measured as change in response time (
Δ
RT) after Diesel Exhaust exposure (
Δ
RT = 22 ms, s.d. = 25 ms), a sample size of 30 subjects will have 90% power to detect significant response time changes of 15 ms assuming the standard significance level of *p* < 0.05. We acknowledge this current study is a different design utilising an older adult population and have, therefore, calculated for a slightly smaller effect size than that of the previous study to compensate for larger RT variance in older adults. As longitudinal studies are prone to extensive participant attrition, the sample size of 45 aims to allow full data to be collected for a minimum of 30 participants. Power calculations were performed using PS [36].

In response to recruitment challenges, we revised the sample size, prompting a re-exploration of the sample size estimate and power calculation to identify the minimum sample likely to yield valuable results. The proposed study design involves comparing the impact of four pollution exposures by examining the differences between pre- and post-exposure measurements relative to baseline measurements. The independent design from the previous study, featuring one measure per group, makes it unfeasible to extrapolate data. Therefore, under the assumption of a conservative correlation among repeated measures set at 0.5, a minimum sample size of 11 participants is needed to achieve 90% power in detecting a moderate (0.45) effect size at a significance level of 0.05.

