#### 2.3.3. Recruitment

Participants will be recruited from the general public. Volunteers who are employees of The University of Manchester or Manchester University NHS Foundation Trust will be permitted to take part if not involved with the project. Advertisement posters will be placed in public spaces including local community groups, places of worship, and NHS and university buildings. Social media advertisements will be run using official accounts of the University of Manchester, NHS Manchester Foundation Trust, and Research for the Future. We will also contact participants who have previously given permission to be contacted for research studies. Due to potential sex-dependent effects of aerosol exposure, we aim to collect equal numbers of biologically male and female participants.

To promote participant retention, participant payment will increase each visit so that there is an increasing incentive to continue participation as the study continues. Informal participant feedback will be collected each visit to improve subsequent visit comfort and amend the protocol as necessary. Data from those who discontinue participation, whether through personal withdrawal or change in eligibility, will be included in data analysis where inclusion of partial data is possible.

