## 3. Discussion

Using an integration of cognitive psychology, atmospheric sciences, clinical experimental medicine, and clinical biochemistry, this project aims to assess the comparative impact of source-specific aerosols on physiological and cognitive functioning. The methodology involves repeated testing pre and post exposure to controlled levels of pollutants, enabling the identification of acute changes in functioning and the detection of peripheral markers of neuroinflammation and neuronal injury.

We initially aimed for 45 participants; however, various recruitment challenges emerged during the study, such as the extended study duration, time-intensive visits, and the eligibility of those in the specific cohort of participants required. Despite efforts to alleviate the burden on participants through protocol reviews and an extensive recruitment drive involving over 45 Patient and Public Involvement and Engagement (PPIE) interactions, it became apparent that recruiting 45 participants was not feasible.

Upon reassessment, the study team adjusted the target to a smaller sample size of 15, assuming a similar dropout rate (33%). This adjustment was made to still maintain sufficient data for reasonable statistical power. Despite this adaptation, we acknowledge that the reduction in statistical power increases the likelihood of not detecting a true effect, leading to a higher risk of committing a Type II error due to wider confidence intervals. Detecting small effects is also challenging due to queries associated with using a shorter exposure time and concentrations relative to previous studies. Similarly, a smaller sample size is more susceptible to random fluctuations, which are anticipated in cognitive functioning. However, the repeated-measures design and control of participant activities during data collection aim to reduce this as a confounding variable.

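### Section 2.7 still permits GEE with about 10 to 15 participants and gives no rule for choosing it; in its usual uncorrected form it would test each pollutant contrast at about 8-12% instead of 5%

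*Protocol article*

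**What the plan says.** Section 2.7 (Data Analysis) commits to longitudinal modelling that allows for repeated measures, and gives as examples "general estimating equation or random effects modelling, depending on the extent and nature of any missing or partial data". It adds that the model will account for drift in pre-exposure values over time and that biological sex will be a covariate. It names no variance estimator and no reference distribution, and it does not say which kind of missingness leads to which model.

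The design (section 2.1) is "sequential controlled exposures to four air pollutants and clean air as control exposure", so each participant can contribute five sessions and there are four contrasts with clean air.

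On size, section 2.3 says "the originally planned sample size was reduced to 15 participants". The Discussion assumes 33% dropout from those 15. Section 2.3.1 states that "a minimum sample size of 11 participants is needed to achieve 90% power". Section 2.3.3 says that data from people who stop early "will be included in data analysis where inclusion of partial data is possible".

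**The concern.** The sandwich variance used by GEE is justified for a large number of independent clusters. Here a cluster is a participant, and there will be between about 10 and 15 of them. At that size the uncorrected estimator is biased downwards, and comparing the Wald statistic with a normal distribution ignores the uncertainty in the variance. Both faults make p-values too small and intervals too narrow. The Discussion treats the smaller sample only as a loss of power with wider intervals. It does not mention that one of the two named models could err in the other direction.

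The second issue is missing data. Unweighted GEE generally needs data missing completely at random, whereas a likelihood-based mixed model needs only missing at random. Under section 2.3.5 eligibility is re-checked at each visit and people who fail are discontinued. The criteria in Appendix A include abnormal spirometry, and lung function is itself a secondary endpoint. Dropout may therefore depend on observed data.

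At stake are the pollutant-versus-clean-air contrasts that support the planned hazard ranking.

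**Working it through.** **Inputs.** Five exposures and four contrasts (section 2.1); 15 recruits and 33% dropout (section 2.3, Discussion); minimum of 11, correlation 0.5, effect size 0.45, significance level 0.05 (section 2.3.1). Assumed, because the article does not say: one analysed value per session (such as the pre-to-post change), two-sided tests, and GEE with uncorrected sandwich errors and a normal reference.

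**1. The plan's own figure.** Section 2.3.1 takes a "conservative correlation among repeated measures set at 0.5" and aims at "detecting a moderate (0.45) effect size at a significance level of 0.05". Reading 0.45 as Cohen's f in a within-participant F test over m = 4 measures, the noncentrality is n·m·f²/(1−ρ), with m−1 and (n−1)(m−1) degrees of freedom.
- n = 11: 11 × 4 × 0.2025 / 0.5 = 17.82, power 92.8%.
- n = 10: 16.2, power 89.6%.

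So 11 reproduces. The article states no type I error for GEE.

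**2. Number of clusters.** 15 × (1 − 0.33) = 10.05, so about 10 completers. Because partial data are kept, the number of clusters lies between about 10 and 15.

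**3. Simple paired contrast, closed form.** With complete data the GEE estimate is the mean within-participant difference, and the sandwich variance is the usual s²/n multiplied by (n−1)/n. A 5% normal test then rejects when |t(n−1)| > 1.96·√((n−1)/n).

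| n | critical value on the t scale | type I error |
|---|---|---|
| 10 | 1.859 | 9.6% |
| 11 | 1.869 | 9.1% |
| 15 | 1.894 | 7.9% |
| 30 | 1.927 | 6.4% |
| 45 | 1.938 | 5.9% |

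Interval width relative to the correct t interval is 1.859/2.262 = 0.82 at n = 10 (18% too narrow) and 1.894/2.145 = 0.88 at n = 15 (12% too narrow).

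**4. With the adjustments section 2.7 points to.** Null simulation with random exposure order, correlation 0.5, exchangeable working correlation correctly specified, sex in the model, and 2,500 datasets (10,000 tests) per cell.

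| Model | n = 10 | n = 11 | n = 15 |
|---|---|---|---|
| exposure + sex | 9.2% | 9.0% | 8.1% |
| + linear session | 10.1% | 10.1% | 8.7% |
| + categorical session | 11.3% | 11.8% | 9.7% |

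Starting from 15 with 33% dropout and categorical session, the result is 11.2%. A separate simulation with Latin-square orders (4,000 datasets per size; exposure, period and sex in the model) gave 11.6%, 10.6% and 8.9% for n = 10, 11 and 15. Together these give about 9-12%.

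**5. Alternatives at n = 10 to 15.**
- GEE with bias-reduced errors and a t(n−1) reference: 3.3-4.6%.
- GEE with bias-reduced errors and a normal reference: 5.2-6.6%.
- Model-based exchangeable errors, close to a random-intercept model: 4.1-5.6%.
- Within-participant least squares with a t reference: 4.7% (n = 10) and 5.3% (n = 15); with dropout, 4.6% and 5.1%.

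**The case against.** The strongest reply is that the article never says uncorrected sandwich errors will be used. GEE appears only as an example, and the variance estimator and small-sample correction are commonly left to an analysis plan that is not shown. GEE with corrected errors and a t reference holds its level here, so GEE as such is not invalid at this size. All of this stands, and it makes the error rates conditional. It does not remove the point: one of the two named models, run in its usual form, is unsuited to the revised sample, and the article sets no rule that would steer away from it.

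A reader might also infer more than the documents support:

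- **That every pollutant interval in this trial will be too narrow.** Random effects is equally permitted and stays near 5%.
- **That choosing the model after seeing the missing data amounts to choosing a p-value.** The stated criterion is missingness, not results, and section 2.3.4 says the staff responsible for analysis are blinded to exposure. The missing rule is a weakness in pre-specification; none of the inflation above comes from it. The clause could even lead the analysts away from GEE when missingness is not completely random, although it does not say so.
- **That the error rate reaches 13% or more.** That requires either applying further dropout to the 10 who remain after dropout, or adding sex-by-exposure terms (10.5% at n = 15, 13.0% at n = 11, 15.2% at n = 10). Section 2.7 lists sex only as a covariate.
- **That the model list was carried over from the 45-participant design.** The article already reports the reduction, so this is conjecture.

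Multiplicity across contrasts and tasks is a separate matter and is not counted here.

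**Conclusion.** The point holds as a conditional one. Section 2.7 leaves GEE open for about 10 to 15 participants with no rule for the choice. If uncorrected sandwich errors and a normal reference are used, the type I error per contrast is about 8-10% for a simple paired contrast and about 9-12% with categorical session adjustment, against a nominal 5%. The closed-form figures assume complete data and normally distributed differences. The simulated ones also assume a correlation of 0.5 and a correctly specified working correlation. GEE carries the stronger missing-data assumption as well, in a trial that expects to lose a third of its participants. The size of any bias from that cannot be derived from the documents. The change should be made, but the documents do not show that the analysis as a whole is invalid.

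**What to change.** State in section 2.7 that the primary model for each cognitive outcome is a linear mixed model fitted by REML, with a participant random intercept, exposure and session as fixed effects, sex as a covariate, small-sample degrees of freedom such as Kenward-Roger, and all available sessions included. Keep GEE, if wanted, only as a sensitivity analysis with a bias-corrected variance (Mancl-DeRouen or Kauermann-Carroll) and a t reference. The dependence of the primary model on the missing-data pattern then goes.

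The cost is one sentence and the matching analysis code, and the model is already one of the plan's two options. Intervals will be somewhat wider than uncorrected GEE would report. On the paired-contrast arithmetic a correct t interval is 2.262/1.859 = 1.22 times as wide at n = 10 and 2.145/1.894 = 1.13 times at n = 15. The Kenward-Roger model itself was not simulated; the support for it comes from the closely related analyses in step 5. A random intercept alone also assumes the same within-participant variance for all exposures, which the GEE sensitivity analysis would help to check.
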